This study will assess the safety and immune response following each of the two doses of Novartis **Influenza A (H1N1) 2009 monovalent vaccine** in HIV-1 infected children and youth in the US and Puerto Rico. Two doses are thought to be required because study subjects have had no prior exposure to **2009 H1N1 Influenza A**. Because seasonal influenza vaccine often results in blunted response in HIV-1 infected persons, we have opted to investigate the higher dose of antigen, 30mcg, in comparison to the 15mcg dose that is currently being studied in ongoing trials of the **Influenza A (H1N1) 2009 monovalent vaccine** in healthy children. We have also opted to stratify our study population into 3 groups based on age. The groups were selected to provide information across all age groups and with knowledge that there would be insufficient power to compare immune response across age groups. This study is limited to HIV-1 perinatally infected children and youth.

In order to understand the mechanism of disease and protection, we will investigate the seroresponse, duration of response, and development of influenza-like illness following vaccine in this population. We also propose investigation of the cell-mediated response to vaccine. The generation of cytotoxic T lymphocyte (CTL) responses against **2009 H1N1 Influenza A** is of particular interest, because this virus replicates better in lung tissue than seasonal influenza and CTLs are the major mediator of viral clearance in the lungs. Memory B cells to **2009 H1N1 Influenza A** will ensure that the host responds adequately to exposure to the wild type virus.

In summary, **2009 H1N1 Influenza A** is likely to infect a significant proportion of HIV-1 infected children and youth if an effective vaccine is not available

before infection is widespread. Infection will likely lead to severe disease in this vulnerable population, therefore, vaccine efforts are critical. Immunogenicity of the candidate **Influenza A (H1N1) 2009 monovalent vaccine** must be established in HIV-1 infected children in order to assure that this population is protected. Lack of a protective immune response would support the need for additional measures to protect this high risk population.

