### 2.2 Secondary Objectives

1. To correlate vaccine response with baseline antibody titer.
2. To assess persistence of antibody response 6 months after Dose #2 of **Influenza A (H1N1) 2009 monovalent vaccine**.
3. To correlate immune responses with CD4+ cell count, CD4%, ARV use, plasma HIV-1 RNA concentration at the time of first immunization, and with timing of seasonal influenza vaccine.
4. To assess cell-mediated immune responses to **Influenza A (H1N1) 2009 monovalent vaccine**.
5. To describe influenza-like illness (ILI) occurring during the course of the study period, through clinic visits for all acute febrile and respiratory illnesses, including collection of respiratory specimens for determination of influenza with RT-PCR.
6. To explore factors related to HIV and its treatment that might affect the responses to H1N1 vaccinations.

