#### 8.212 Adverse Events of Grade 3 or higher severity attributed to the study vaccine.

#### 8.213 Second vaccine dose withheld, due to adverse reactions attributed to first dose.

#### 8.214 Immunologic response, defined as HAI titer $\geq 1:40$ , at 21 days after Dose #1 and at 10 days after Dose #2.

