### 8.4 Sample Size and Accrual

Approximately 140 children and youth, aged  $\geq 4$  years to 25 years old, who were infected with HIV-1 via perinatal transmission will be enrolled into this study. We will enroll at least 40 subjects each from three different age groups: age  $\geq 4$  years to  $< 9$  years of age,  $\geq 9$  years to  $< 18$  years of age and  $\geq 18$  to  $< 25$  years of age. This sample size is expected to yield at least 120 evaluable\* subjects, which will provide reasonably precise estimates of rates of adverse events and immunogenic response. Evaluable subjects are defined as having received two doses of Novartis **Influenza A (H1N1) 2009 monovalent vaccine** 21-28 days apart and had all HAI samples for collected up to and including Day 10 post second dose within the protocol specified windows.

Accrual is anticipated to be 4-6 weeks.

\*Evaluable subjects are defined as having received two doses of Novartis **Influenza A (H1N1) 2009 monovalent vaccine** 21-28 days apart and had all HAI samples for collected up to and including Day 10 post Dose #2 within the protocol specified windows.

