#### 8.612 Immunogenicity

The proportion of subjects meeting the criteria for immunologic response following the first and second vaccine doses will be presented. The precision with which this sample result estimates the rate of immunologic response rates in the population represented by the study sample will be reported in terms of 90% CIs around the sample proportions. This will provide 95% confidence that the rate of

immune response is not less than the lower limit of the proportion of study subjects meeting immune response criteria.

Table 3 illustrates the confidence intervals for a range of hypothetical proportions of immunologic response. This table shows (e.g.) that a sample finding of 90 responders in the total sample of 120 subjects (75%) would provide 95% confidence that the rate in the population from which the sample was drawn was no lower than 68%. If a subsample of 20 subjects exhibited a 75% response rate, this would provide 95% confidence that the population rate was no lower than 54%.

**Table 3: Exact 90% Confidence Intervals around Potential Proportions of Subjects Meeting Immunologic Response Criteria (Total Sample and Selected Subsample Sizes)**

| N   | Sample rate | Lower Limit | Upper Limit |
|-----|-------------|-------------|-------------|
| 120 | 25%         | 19%         | 32%         |
|     | 50%         | 42%         | 58%         |
|     | 75%         | 68%         | 81%         |
|     | 90%         | 84%         | 94%         |
|     | 95%         | 90%         | 98%         |
| 40  | 25%         | 14%         | 39%         |
|     | 50%         | 36%         | 64%         |
|     | 75%         | 61%         | 86%         |
|     | 90%         | 79%         | 97%         |
|     | 95%         | 85%         | 99%         |
| 20  | 25%         | 10%         | 46%         |
|     | 50%         | 30%         | 70%         |
|     | 75%         | 54%         | 90%         |
|     | 90%         | 72%         | 98%         |
|     | 95%         | 78%         | 99.7%       |

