## 8.62 Key Secondary Analyses

Prediction of immune response will be addressed in secondary analyses. Since this is a new vaccine about which there is considerable uncertainty with respect to the distribution of antibody titers which it may elicit, alternative outcome variables will be explored. These include:

- 1) The log (10) HAI titer,
- 2) HAI titer >10, considered indicative of an immune response; and
- 3) HAI titer >40, which is considered to be likely to be protective.

The distribution of log (10) HAI titer will be examined to determine whether it satisfies the normality assumption required for linear regression analysis. If this is not true, then this method will be not be used. Since the other potential outcome

variables listed above are categorical, the method of analysis for those outcome variables will be logistic regression.

Factors predicting immune response will be examined on data collected after the first vaccination and, again, after the second. A primary predictor will be the age stratification factor. If immune response were to vary significantly across age strata, this would counter indicate pooling across age strata when presenting results. Additional potential predictors will include variables such as: CD4 count or percentage at baseline, viral load at baseline, HAI titers to the seasonal influenza vaccine, ARV treatment, and timing of seasonal influenza vaccine. Additional predictors may be explored as additional data concerning the H1N1 virus and the study vaccine become available.

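### An HAI titer of at least 1:40 after vaccination is labelled vaccine response without reference to baseline, so subjects already at that level on entry count as responders

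*Combined protocol and SAP*

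**What the plan says.** **Endpoint and primary analysis.** Section 8.214 gives the primary endpoint as "Immunologic response, defined as HAI titer" of at least 1:40, 21 days after Dose #1 and 10 days after Dose #2. Section 8.612 then states: "The proportion of subjects meeting the criteria for immunologic response following the first and second vaccine doses will be presented". Precision "will be reported in terms of 90% CIs around the sample proportions", and the lower limit is read as a one-sided 95% bound on the immune response rate. Neither section conditions on, or splits by, the baseline titer.

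**Other antibody measures.** The secondary endpoint (8.221) is again a titer of at least 1:40. The geometric mean titers in 8.231 are post-dose only. The alternative outcomes in 8.62 (log titer, titer above 10, titer above 40) do not refer to baseline. No fold-rise or seroconversion measure appears anywhere. By contrast, 8.62 does compare ELISPOT counts with baseline, using paired tests.

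**Baseline titer.** Secondary objective 1 (section 2.2) is "To correlate vaccine response with baseline antibody titer". Baseline 2009 H1N1 HAI is scheduled at screening (section 3.0; Appendix IA, footnote 14). The predictors named in 8.62 are age stratum, CD4, "viral load at baseline, HAI titers to the seasonal influenza vaccine, ARV treatment" and timing of seasonal vaccine. Baseline 2009 H1N1 HAI is not named, although the list is expressly open to additions.

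**Prior immunity.** Section 1.22 states that children and young adults have no protective titers. It also says that "study subjects have had no prior exposure to" the virus, although there the statement justifies giving two doses. The same section expects spread to increase strongly in the coming season. Exclusion 4.23 covers PCR-proven illness or any positive influenza test since June 2009. Section 8.1 accepts that background exposure differing between sites may affect response.

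**The concern.** There is no control arm, so the subject's own baseline is the only reference for what the vaccine did. A subject at 1:40 or above on Day 0 who gains nothing from either dose still counts as a responder. The endpoint measures vaccine response only when such subjects are rare. The protocol assumes that they are rare but does not ensure it, because there is no serologic screen and an untested or subclinical infection passes exclusion 4.23.

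Three uses of the result depend on this:

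- The bound in 8.612 is worded as a bound on immune response. Read as vaccine response, it is too high if s is appreciable.
- Section 8.62 lets variation in response across age strata decide whether strata are pooled. If s differed by age, prior infection could drive that decision.
- Section 1.22 says a lack of protective response would support further measures for this population. A headline rate that includes existing immunity says less about whether the vaccine supplied the protection.

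There is also a gap between objective and analysis. Secondary objective 1 has no specified method. If it is answered with the 1:40 outcome, the association is partly automatic, because those at or above 1:40 on entry are already responders unless their titer falls.

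**Working it through.** **Inputs.** N = 120: "This sample size is expected to yield at least 120 evaluable" subjects (section 8.4). The worked example in 8.612 is "a sample finding of 90 responders in the total sample of 120 subjects (75%) would provide 95% confidence" of a rate no lower than 68%. The baseline share s at or above 1:40 is not in the documents, so it is an assumption, taken from 0% to 30%. The response rate r among subjects below 1:40 at baseline is also unknown, and is taken at 25%, 50%, 75% and 90%, all of which are rows of Table 3.

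**Step 1: the plan's figure.** The exact (Clopper-Pearson) 90% interval for 90/120 is 67.65% to 81.39%, matching the stated 68% to 81%. All 15 rows of Table 3 reproduce to rounding. The arithmetic is sound, and the question is what the proportion measures.

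**Step 2: size of the overstatement.** Assume baseline positives remain at or above 1:40. Then

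observed rate = s + (1−s)r, and overstatement = observed − r = s(1−r).

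For example, s = 20% and r = 50% give 0.20 + 0.80 × 0.50 = 60%, an excess of 10 points.

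| r | s = 0% | s = 10% | s = 20% | s = 30% |
|---|---|---|---|---|
| 25% | 0 | 7.5 | 15 | 22.5 |
| 50% | 0 | 5 | 10 | 15 |
| 75% | 0 | 2.5 | 5 | 7.5 |
| 90% | 0 | 1 | 2 | 3 |

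(Percentage points.)

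**Step 3: against the plan's precision.** At N = 120 and an observed 50%, Table 3 gives 42% to 58%, a half-width of 8 points. With r = 50% and s = 10%, the 5-point excess is smaller than that. With s = 20%, the expected count is 72/120 = 60%, exact 90% interval 52.1% to 67.5%, which excludes the 50% in subjects below 1:40 at baseline. With r = 75%, the excess at s = 20% is 5 points, against a half-width of (81 − 68)/2 = 6.5.

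**Step 4: the plan's example by baseline status.** Remove the 120s baseline positives from both numerator and denominator of 90/120.

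| s | Rest of sample | Rate | Exact 90% interval |
|---|---|---|---|
| 0% | 90/120 | 75.0% | 67.7% to 81.4% |
| 5% | 84/114 | 73.7% | 66.0% to 80.4% |
| 10% | 78/108 | 72.2% | 64.3% to 79.2% |
| 20% | 66/96 | 68.8% | 60.1% to 76.5% |
| 30% | 54/84 | 64.3% | 54.8% to 73.0% |

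In an age stratum of 40 with 30 responders (75%, lower limit 61.3%), s = 20% leaves 22/32 = 68.8%, lower limit 52.8%.

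**The case against.** The strongest reply is that the endpoint answers the question the protocol asks. Section 8.62 treats 40 as a likely protective level, and section 1.22 wants to know whether this population is protected. The share at or above 1:40 after vaccination answers that wherever the antibody came from. This stands: the endpoint is legitimate as seroprotection, and the fault lies in the label and the missing baseline context.

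The size may also be nil. The protocol's only statement on this age range is that protective titers are absent, and exclusion 4.23 is broad, since a positive influenza test need not be specific to H1N1. This stands too: at s = 0 there is no bias, and when r is high the bias is small even at s = 30%. It does not remove the point, because s will be measured and the plan does not commit to reporting it.

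Stronger readings that a reader might infer are not supported:

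- *The primary endpoint is invalid and seroconversion must replace it.* The documents support seroprotection as an aim and give no seroconversion cut-off. In a single-arm study during a pandemic, a rise from baseline can also come from infection between Day 0 and the last sample, so it does not isolate the vaccine either.
- *The plan rules out baseline H1N1 titer as a predictor.* The 8.62 list is illustrative and can be extended. What is missing is a specified analysis for a stated objective.
- *Age comparisons are confounded.* Nothing in the documents shows that s differs by stratum, and section 1.22 disclaims power for such comparisons. The possibility matters only because 8.62 ties pooling to them.

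**Conclusion.** The point holds in a limited form. As written, 8.214 and 8.612 would count subjects already at or above 1:40 as vaccine responders, and no other antibody measure in the plan would reveal it. The proportion is sound as seroprotection, but as a vaccine-response rate it is sound only if s is near zero.

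The textual gap is certain; the size of any bias is not. Over s from 0% to 30% and r from 25% to 90%, the overstatement runs from 0 to 22.5 points. It is largest where true response is poor, which is the case of most concern in a population that section 1.22 expects may respond weakly. These figures assume that baseline positives stay at or above 1:40 after vaccination. The change should be made, but the gap does not undermine the trial, because the data needed to close it are already scheduled.

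**What to change.** 1. **Section 8.214:** keep a titer of at least 1:40 as the primary endpoint, and label it seroprotection.
2. **Section 8.612:** report the proportion at or above 1:40 at baseline. Give the post-dose rate with its 90% interval separately for subjects below 1:40 and at or above 1:40 at baseline, overall and by age stratum. Read vaccine response from the group below 1:40.
3. **Section 8.22 or 8.23:** add a baseline-referenced measure as secondary, such as a fold-rise with a stated threshold. Four-fold is one example; the documents give none, so the sponsor must choose and justify it.
4. **Section 8.62:** name log baseline 2009 H1N1 HAI as a predictor, including in the age-stratum comparison that informs pooling. Answer secondary objective 1 with fold-rise or within the subset below 1:40 at baseline.

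**Cost.** Wording and a few table columns, with no new visits, blood draws or subjects. The group below 1:40 is smaller and its interval wider: at s = 20%, N falls from 120 to 96 and, in the plan's example, the interval widens from 13.7 points (81.4 − 67.7) to 16.4 points (76.5 − 60.1). The response rate may look less favourable. Any rise from baseline should carry the caveat that infection during the study can also produce it.

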### 8.22 Secondary endpoints

#### 8.221 HAI $\geq 1:40$ at 6 months after Dose #2.

### 8.23 Secondary response variables

#### 8.231 Geometric Mean Antibody Titers (GMT) HAI following: 1) Dose #1 and Dose #2, and 2) at 6 months after Dose #2.

- 8.232 Cell-mediated immune responses, as measured by B-cell and T-cell ELISPOT values and frequency of cytotoxic T cell lymphocytes specific for **2009 H1N1 Influenza A virus**.
- 8.233 HAI titers against seasonal influenza viruses containing TIV.
- 8.234 Cell-mediated immune responses to influenza viruses contained in TIV and other antigens.

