### 1.22 Justification Discussion

It is very likely that the continuing epidemic spread of **2009 H1N1 Influenza A** infection in the US will greatly increase in the fall-winter season when social interactions and climactic conditions become even more conducive to spread of influenza viruses. While reports to date suggest that healthy individuals typically have a mild illness, underlying medical conditions including immunodeficiency appear to increase risk for severe disease and even death with pandemic H1N1 (48). Thus, knowledge of the safety and immunogenicity of the **Influenza A (H1N1) 2009 monovalent vaccine** in HIV-infected children and youth is critically important to address the health care needs of this vulnerable population.

Because seasonal influenza has been shown to cause more severe illness in HIV-infected individuals compared to that typical of age-matched uninfected people (33;34), it is likely that **2009 H1N1 Influenza A** will result in significant morbidity and possibly mortality in HIV infected individuals. Morbidity may be a direct result of the influenza virus or infection may result in secondary bacterial infections or decreased adherence to the patient's antiretroviral therapy due to the severe nausea and vomiting that may occur with pandemic H1N1 illness. Prevention of infection in this population will be critical.

It is well established that seasonal influenza infection impacts children in a community before becoming widespread in adult populations. Susceptibility to disease among young populations appears even more pronounced with **2009 H1N1 Influenza A** as one third of older adults have measurable levels of serum HAI or neutralizing antibody against the **2009 H1N1 Influenza A** while young adults and children completely lack protective titers. The serologic data is consistent with the observation that the attack rate and disease severity for the virus appears to be much higher in younger populations with relative protection of those >50 years of age.

Efforts are currently underway to evaluate **Influenza A (H1N1) 2009 monovalent vaccine** in healthy children. However, HIV-1 infected children attend schools and participate in all the activities that typically put children at such high risk for infection with influenza. Protection of HIV-1 infected children and youth from **2009 H1N1 Influenza A** will require knowledge of safety and immunogenicity of these new products in this population.

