#### 4.51 Vaccines

Receipt of any vaccines besides the study product will be collected throughout the study from enrollment to the off study visit. The administration of inactivated licensed vaccines, including inactivated seasonal influenza TIV, should be at least

2 weeks (14 days) before Dose #1 or delayed until the STEP II Day 10 visit has occurred and immunogenicity samples have been collected.

The administration of live licensed vaccines, including seasonal cold-adapted live influenza vaccine, should be at least 4 weeks (28 days) before Dose #1 or delayed until at least the STEP II Day 10 visit has occurred and immunogenicity samples have been collected.

If administration of the seasonal influenza vaccine outside of the windows described above is necessary for clinical care, the investigator should notify the protocol team at [[contact]](mailto:[contact]). The seasonal influenza vaccine is not provided by this study.

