## 6.2 Subject Management

Subjects will remain in the clinic for at least 30 minutes after each vaccination so that clinic personnel can observe for adverse reactions to the vaccine. Subjects will be contacted by telephone or other methods on Day 2 ( $\pm 1$  day) and Day 10 ( $\pm 3$  days) after Dose #1 and then again on Day 2 ( $\pm 1$  day) after Dose #2 for reactogenicity assessments and interview. Additionally, subjects will be seen on Day 10 ( $\pm 3$  days) after Dose #2 for reactogenicity assessments and safety monitoring (see Appendix IA and IB).

NOTE: A clinic visit is required within 24 hours for any new onset of weakness of legs, tingling of hands and/or feet, or difficulty walking.

In addition, all subjects except women who become pregnant after Dose #1 but prior to Dose #2 (see Appendix IA & IB) will be seen and evaluated 7 months after Dose #1; data will be collected for any signs and symptoms related to Guillain-Barré Syndrome, and other serious adverse events.

The Guillain-Barré Syndrome monitoring tool questionnaire to be completed at the clinic may be accessed by going to the [www.fstrf.org](http://www.fstrf.org) website and clicking on the QUALITY OF LIFE link. The form is labeled 'GBS Baseline and Monitoring Tool – II'.

Subjects should be asked to return to clinic for an unscheduled clinic visit, within 24 hours of development of symptoms consistent with Guillain-Barré Syndrome, such as new onset of weakness of legs, tingling of hands and/or feet, or difficulty walking (see section 6.6).

Subjects will also be asked to return to clinic within 72 hours for assessment for any of the following:

- Assessment of grade 3 or 4 possibly vaccine associated events
- Suspected serious adverse events (other than Guillain-Barré Syndrome),
- Symptoms consistent with influenza-like illness (ILI) (see section 6.5)

It is anticipated that vaccine-associated AEs will occur frequently, but that these will be minor local reactions and side effects that will rarely necessitate interruption of the vaccination schedule. Management of adverse experiences will be according to the best clinical practice and the judgment of the site investigator.

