## 8.0 STATISTICAL CONSIDERATIONS

### 8.1 General Design Issues

This is a Phase II study in children and youth  $\geq 4$  years to  $< 25$  years old who were infected with HIV-1 via perinatal transmission. This study is designed to investigate the safety, reactogenicity, and immunogenicity of a two dose regimen of Novartis **Influenza A (H1N1) 2009 monovalent vaccine**.

The sample will be stratified into 3 age strata, which may differ with respect to immune response. Moreover, factors such as immune status at the time of first immunization and differences in background exposure to the virus across sites participating in the study

may have an impact on response to the vaccine. The study will not have an adequate sample size to provide precise estimates of immune response and adverse events rates for all subgroups which may exhibit differing results. Section 8.6 presents confidence intervals around potential subgroups of various sizes with a range of potential results to provide an indication of the precision with which these rates can be estimated.

The study will be monitored intensely by the protocol team, which will review data every other week while subjects are accruing and the vaccine is being administered and at least once a month after the last dose of study vaccine has been administered (See Section 8.5). A Safety Monitoring Committee (SMC) will be convened by IMPAACT to review safety information gathered from all study participants.

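### The 6-month persistence endpoint counts H1N1 antibody from any source, so infection or further vaccination after Step II Day 10 can only push apparent persistence of the vaccine response upward

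*Combined protocol and SAP*

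**What the plan says.** Section 2.2 sets the aim: "To assess persistence of antibody response 6 months after Dose #2". The matching endpoint in 8.22 is "8.221 HAI $\geq 1:40$ at 6 months after Dose #2", and 8.231 lists the GMT at 6 months. Neither requires a response at Step II Day 10, and neither refers to intervening H1N1 infection or vaccination. The sample comes from the final visit, at which subjects "will be seen and evaluated 7 months after Dose #1" (section 6.2).

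On exposure, section 1.22 considers it very likely that "infection in the US will greatly increase in the fall-winter season". Section 8.1 recognises that "differences in background exposure to the virus across sites participating in the study" may affect response.

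On other vaccines, section 4.51 asks that licensed inactivated products be given no later than 14 days ahead of the first study dose, or else be "delayed until the STEP II Day 10 visit has occurred and immunogenicity samples have been collected". Live licensed vaccines are held to the same later point. Seasonal vaccines are the named examples; 2009 H1N1 vaccine is not mentioned. Item 1 of the Summary of Changes states that the Novartis H1N1 vaccine is now licensed.

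Documented infection bars Dose #2 if it occurs between Steps I and II (4.412, 6.2, 6.5). Nothing is said about infection after Dose #2. The definition of an evaluable subject stops at Day 10 after Dose #2. Section 8.612 analyses response after each dose, and the only 6-month analysis described in 8.6 concerns memory B cells.

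**The concern.** The objective asks how long the vaccine response lasts, but the endpoint measures who has antibody at 6 months. The two differ for a subject whose titer fell below 1:40 and was then raised again by wild-type virus or a further H1N1 vaccine. That subject is counted as persistent. The reverse error does not arise from re-exposure, so the bias has one direction. It also grows as true persistence falls, because more subjects are then open to misclassification. Section 1.22 says that a lack of protective response would support additional measures for this population, so an overstated persistence figure could weaken that case.

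**Working it through.** **The plan's own precision.** Table 3 gives an exact 90% interval of 42% to 58% for a 50% rate at N = 120. Clopper-Pearson for 60/120 gives 42.1% to 57.9%, which agrees. Its worked example, 90/120, gives 67.7% to 81.4%, against the printed 68% to 81%. No stated figure is wrong.

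**Length of the unprotected interval.** From Appendix IA, Dose #2 falls 21 to 28 days after Dose #1, the Step II Day 10 sample 7 to 13 days later, and the last sample 6 to 8 months after Dose #1. With 30-day months:
- shortest: 180 − (28 + 13) = 139 days, about 4.6 months
- longest: 240 − (21 + 7) = 212 days, about 7 months

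**Size of the bias.** Let p be true persistence of the vaccine response and a the share re-exposed in that interval. The documents give neither, so both are assumptions. If every re-exposed subject reaches and holds 1:40 (the worst case), the observed rate is p + a(1 − p) when exposure is independent of titer, and p + a when it falls only on waned subjects. For p = 50%:

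| a | Independent | Waned only |
|---|---|---|
| 5% | 52.5% | 55% |
| 10% | 55% | 60% |
| 20% | 60% | 70% |

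Under independence with a = 20%, p = 25% becomes 40% and p = 75% becomes 80%.

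**Against sampling error.** An observed 72/120 (60%) has a 90% interval of 52.1% to 67.5%, which excludes the assumed truth of 50%. Under independence and N = 120, the lower limit first passes the true rate at a of about 10% (p = 25%), 17% (p = 50%) or 30% (p = 75%).

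**How candidate corrections behave.** With perfect detection of re-exposure:
- *Excluding re-exposed subjects* gives p(1 − a)/(1 − a) = p under independence, and p/(1 − a) if only waned subjects are exposed. At p = 50%, a = 20% these are 50% and 62.5%.
- *Counting them as not persistent* gives p(1 − a) under independence, and p if only waned subjects are exposed. At p = 50%, a = 20% these are 40% and 50%. At p = 75%, a = 20% under independence it gives 60%, while the as-measured figure is 80%.

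Each recovers p under one exposure pattern and misses it under the other. Neither can stand alone.

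**The case against.** The strongest defence is that 8.221 is a plain seroprotection proportion: secondary, single-arm and descriptive, with no hypothesis or decision rule. Non-study vaccines are recorded to the end of study (4.51), influenza-like illness is tested by RT-PCR (6.5), and H1N1 titers are run at every sampling visit (Appendix IA, footnote 14). A careful author could interpret the result alongside these data. That is true and limits the seriousness, but the stated objective is persistence, and no rule says how the data would be used.

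Several stronger readings are tempting and are not supported:

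- *That 4.51 expressly releases H1N1 vaccine after Day 10.* It does not name it. H1N1 vaccine is reached only as a member of the licensed class, and nothing suggests that subjects who have had two study doses would commonly seek another. Seasonal vaccine, which 4.51 does name, is described in section 1.1 as unlikely to protect against the new virus. Wild-type exposure alone is enough for the point.
- *That 10% re-exposure necessarily carries the estimate past its error bar.* Under independence it gives 55%, inside 42% to 58%. It reaches 60% only if exposure falls wholly on waned subjects.
- *That a failing response would be reported as durable.* A shift from 50% to 55% or 60% does not show that, and the upper bounds assume that every re-exposed subject responds fully, although sections 1.1 and 1.22 describe blunted vaccine responses in HIV infection.
- *That a titer rise between the two samples identifies the re-exposed.* Someone at 1:160 on Day 10 who wanes to 1:20 and is boosted back to 1:160 shows no net rise. If that infection was silent, RT-PCR misses it too.
- *That a figure counting all re-exposed subjects as failures should be the headline.* At p = 75%, a = 20% under independence it is 15 points too low, while the as-measured figure is 5 points too high.

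**Conclusion.** The point holds as a mismatch between objective and endpoint, with an upward bias whose size the documents do not determine. At an assumed true persistence of 50%, re-exposure of 5% to 20% adds at most 2.5 to 10 points if exposure is independent of titer, and at most 5 to 20 points if it is confined to waned subjects. These figures rest on assumed attack and outside-vaccination rates and on every re-exposed subject reaching 1:40. The conclusion needs only that some waned subjects are re-exposed, which the protocol's own expectation of spread makes plausible. The 6-month GMT has the same weakness. The primary immunogenicity endpoints, measured at or before Step II Day 10, are not affected by exposure after that visit.

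**What to change.** Keep 8.221 as measured and label it seroprotection from any source. Add to 8.6 a written analysis of the 6-month HAI data with a prespecified sensitivity analysis. Flag a subject as re-exposed after Step II Day 10 on any of:

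- (a) RT-PCR-confirmed 2009 H1N1 infection;
- (b) recorded receipt of non-study 2009 H1N1 vaccine;
- (c) a rise of at least 4-fold in H1N1 HAI titer from Step II Day 10 to 7 months.

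Report 8.221 three ways: as measured, with flagged subjects excluded, and with flagged subjects counted as not persistent. Describe the last as a conservative figure, not the headline. Report the 6-month GMT with and without flagged subjects, and give the number flagged under each criterion.

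The cost is analysis wording; no new visit, sample or assay is needed. Two limits should be stated with the results. Silent infection that restores a waned titer without a net rise goes undetected, so some upward bias can remain. Criterion (c) may flag late vaccine responders, because its baseline is drawn only 7 to 13 days after Dose #2.
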